However, one of the noted drawbacks of SDF application is its potential to cause discoloration of the teeth and oral tissues [17]. Black staining is an often-reported side effect of SDF application and influences the acceptability of this therapy. The use of potassium iodide (KI) directly after SDF application results in masking the staining of the affected dentine [23]. Applying KI over SDF creates an insoluble layer of yellow precipitate of silver iodide, thus obscuring the black staining on the tooth [24]. The effectiveness of SDF in preventing caries progression was not affected by the application of KI [25]. The application of saturated potassium iodide solution to reduce discoloration was not found to be effective in altering or preventing caries in a study among community-dwelling senior citizens [26].

Due to their safety, efficiency, feasibility, and effectiveness in dental caries management, ART and SDF are employed in routine treatments for all age groups. Yet if the initial prevention strategies fail, there is a need for effective management to arrest the disease, restore the cavitated tooth, and reduce the negative impact of caries lesions. The silver modified atraumatic restorative technique, known as the SMART technique, is a modification of ART, as stated in a case report, wherein the application of SDF is followed by conditioning with polyacrylic acid and restoration of the cavitated tooth with GIC [27]. By using SMART with chemically sealed restoration, the nutrient source for any persistent bacteria is cut off, thus killing the microbes, arresting and remineralizing the caries dentin, preserving the remaining tooth structure, and enhancing the pulp vitality [27]. The application of an antimicrobial agent like SDF before the placement of a restoration proved to be more effective, slowing the progression of the carious lesion [28]. There are no reports which suggest hampering of shear bond strength of glass ionomer cement to carious dentine by the application of KI solution after SDF placement [29,30].

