### 2.7. Interventions

After patient selection, the treatment will be given to the patient according to the selection process. The study participants will be allocated to either one of two parallel arms.

Study arm 1: will receive SDF application and ART restoration.

Study arm 2: will receive ART restoration.

All treatment will be done in a dental chair.

At the baseline visit, an assessment of cavitated caries lesions will be done on all the study participants. The ADA Caries Risk Assessment Form (Age > 6) would be used to assess the risk. Depending on the study arm, ART with or without SDF will be applied to selected teeth (Figure 1). The demographic features of participants and their caries status will be recorded.

*Procedure to be followed for study arm 1:*

A preoperative photograph of the selected tooth will be taken. The caries lesion entrance will be widened and with help of a dental hatchet, the thin unsupported frangible enamel will be removed. In the next step, the decayed tissue will be excavated with a spoon excavator, first at the dentin enamel junction and thereafter from cavity walls and the pulpal floor. The cavity will then be rinsed with water and air-dried, followed by isolation with cotton rolls.

*Application of Silver Diamine Fluoride*

Using a disposable micro applicator tip, the SDF (e-SDF, 38% silver diamine fluoride, Kids-e-dental LLP, Globus Medisys, Mumbai, India) will be applied to the walls of the prepared cavity for 10 s and allowed to air dry for one minute. One drop of 38% SDF solution (2.24 F-ion mg/dose) would be required per tooth. A saturated solution of potassium iodide (Lugol’s Iodine solution 5%, Bio balance, Pali Marwar, Rajasthan, India) will be applied with a different microsponge to decrease color change and will be repeated 1-3 times until no further black discoloration is observed [17].

*Placement of ART restoration*

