Glass ionomer cement (Glass Ionomer High Strength Posterior restorative, GC Corporation, Tokyo, Japan) will be prepared according to the manufacturer’s instructions. The restorative material will be placed into the prepared cavity using a plastic filling instrument. The press finger technique will be used for approximately one minute and the restoration will be coated with petroleum jelly. A carver would be used to remove the excess material. The height of restoration will be adjusted after the bite is checked using articulation paper. A photograph and a digital radiograph of the restored tooth will be taken after the procedure and at the end of the study.

*Procedure to be followed for study arm 2:*

*Placement of ART restoration*

A preoperative photograph of the selected tooth will be taken. The preparation of the cavity will be done as stated above using hand instruments. Conditioning of the prepared tooth surface will be done with an applicator tip saturated with the polyacrylic acid liquid for 10–15 s. Glass ionomer cement (GIC Fuji IX, G C CORPORATION, [name]) will be prepared according to the manufacturer’s instructions and placed into the cavity using a plastic filling instrument. The press finger technique will be followed, and the surface of the restoration will be coated with petroleum jelly. The bite will be checked using articulation paper and the occlusal adjustments will be done. A photograph and a digital radiograph of the restored tooth will be taken after the procedure and at the end of the study.

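### As written, only the ART-alone arm has its cavities conditioned with polyacrylic acid, so a difference in restoration survival could not be attributed to adding SDF (with potassium iodide) to the same ART

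*Protocol article*

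**What the plan says.** Section 2.7 of the protocol article defines the contrast: "Depending on the study arm, ART with or without SDF will be applied to selected teeth". It then sets out each arm's procedure.

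- **Arm 1.** After excavation, rinsing, drying and isolation, SDF is applied, followed by potassium iodide ("A saturated solution of potassium iodide"). The placement part then opens with the cement itself: "Glass ionomer cement (Glass Ionomer High Strength Posterior restorative, GC Corporation, Tokyo, Japan) will be prepared according to the manufacturer". No conditioning is mentioned.
- **Arm 2.** Cavity preparation is carried over from arm 1 ("The preparation of the cavity will be done as stated above using hand instruments"). The next step is "Conditioning of the prepared tooth surface will be done with an applicator tip saturated with the polyacrylic acid liquid", for 10–15 s. Only then comes the cement, under a different label: "Glass ionomer cement (GIC Fuji IX, G C CORPORATION".

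The Introduction describes the published combined technique (SMART) as one in which "the application of SDF is followed by conditioning with polyacrylic acid and restoration of the cavitated tooth with GIC".

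Survival of the restoration is listed under Primary Outcomes (section 2.8.1) and is a stated aim at the end of the Introduction. Section 4 compares it between arms with Kaplan–Meier curves and a log-rank test, and examines factors affecting it by Cox regression.

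**The concern.** A trial of ART with or without SDF needs the ART component to be the same in both arms. Here a step in placing the restoration is written for one arm only, and that restoration's survival is a primary outcome. If operators follow the text, a survival difference reflects SDF, potassium iodide and the absence of conditioning together.

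Potassium iodide is also confined to arm 1, but the protocol openly describes it as part of the SDF application. The intended contrast is therefore fairly read as SDF + potassium iodide + ART against ART. Conditioning is different: the protocol places it within ART in arm 2 and within the combined technique in the Introduction.

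Caries arrest is affected only indirectly. Section 2.8.1 judges arrest under a restoration that is still intact, and section 2.8.2 takes the six-month radiograph on restorations that have survived. The rationale in the Introduction also relies on the seal, in a technique that includes conditioning: "By using SMART with chemically sealed restoration, the nutrient source for any persistent bacteria is cut off".

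**Working it through.** **Inputs.** The procedures come from section 2.7, the planned numbers from section 2.11 and the analyses from section 4.

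**The plan's own figure.** Section 2.11 states 100 per group for an effect size of 0.4, alpha 0.05 and 80% power. Sidedness is not stated; two-sided is assumed here.

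- Normal approximation: n = 2 × (1.960 + 0.842)² / 0.4² = 2 × 7.85 / 0.16 ≈ 98.1, so 99 per group.
- t-test version: 99.08, so 100 per group.
- Attrition of 10%: 100 × 1.1 = 110, and 99 / 0.9 = 110. Dividing 100 by 0.9 would give 112.

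The figure reproduces. It is used below only for the planned count of 110 per arm, and adding a conditioning step changes none of its inputs.

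**The two procedures side by side.**

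| Step | Arm 1 | Arm 2 |
|---|---|---|
| Hand-instrument cavity preparation | described | carried over from arm 1 |
| SDF, 10 s, then one minute drying | yes | no (intended) |
| Potassium iodide, 1–3 times | yes | no (declared part of the SDF step) |
| Polyacrylic acid, 10–15 s | **not stated** | **stated** |
| Glass ionomer, finger press, petroleum jelly, bite check | yes | yes |

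**Does any wording bring conditioning into arm 1?** Two phrases might, and neither does.

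1. The back-reference in "The preparation of the cavity will be done as stated above using hand instruments" sits in arm 2, points from arm 2 to arm 1, and covers cavity preparation only. It cannot move a later arm 2 step into arm 1.
2. The reference to the manufacturer's instructions concerns preparing the cement and appears in both arms. Arm 2 still lists conditioning as a separate step, so the authors did not treat it as covered by that phrase.

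**What the analysis can and cannot separate.** Let A = 1 for arm 1 and C = 1 for a conditioned cavity. As written, C is 1 for 110 of 110 participants in arm 2 and for 0 of 110 in arm 1. So C = 1 − A for every participant and every tooth, a correlation of −1. Suppose, for illustration, that the effects add on the log-hazard scale, with β for SDF plus potassium iodide and γ for conditioning:

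βA + γC = βA + γ(1 − A) = γ + (β − γ)A

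The constant γ is absorbed in the baseline hazard, and the data identify only β − γ. The log-rank test compares the same two groups and has the same limit.

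- If γ = 0, the arm contrast equals β and there is no bias.
- If γ < 0 (conditioning reduces failures), then β − γ > β, and the contrast is shifted against the SDF arm.

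The document gives no value for γ, so no size of bias is calculated.

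**The case against.** The strongest objection is that silence in these procedure lists is weak evidence that a step is withheld, because the lists are visibly uneven. Cocoa butter to protect the soft tissues appears only under Adverse Events (section 2.14), not in the arm 1 procedure. The one-minute press and the carver are written for arm 1 only, yet nobody would conclude that arm 2 restorations go untrimmed. The text is a journal article that condenses a fuller protocol. Its framing throughout is one ART given with or without SDF, and the combined technique it describes includes conditioning. On this view the omission is a reporting slip.

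It is also fair to say that perfect collinearity holds for any step given in one arm only, that no passage says conditioning affects survival, and that the randomised comparison itself is intact.

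Much of this stands. It makes a drafting slip more likely, and it rules out any claim about how large a bias would be. It does not remove the point. This is more than a detail left out for brevity: the step is stated for one arm and not for the other in parallel procedures, and no sentence settles the matter. Anyone following the text would deliver two different restorations. Potassium iodide is not a parallel case, because it is declared as part of the SDF application. Whether the two cement labels denote one product cannot be settled from the document, and the point does not depend on it.

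**Conclusion.** The concern holds as a statement about the text as written, and it should be fixed. Section 2.7 gives polyacrylic acid conditioning to every arm 2 participant and to no arm 1 participant (110 and 0 as planned), in conflict with the protocol's own description of the contrast. The comparison of the two packages as delivered remains valid. What is lost is attribution of a survival difference to adding SDF, with potassium iodide, to the same ART.

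This rests on two conditions. The first is that operators follow the written procedure; if arm 1 is in fact conditioned, only the text is wrong. The second is that conditioning has some effect on survival; if it has none, nothing is biased. The document settles neither, so direction and size remain unknown. Confidence is moderate because a drafting slip is plausible.

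**What to change.** - In section 2.7, add to arm 1, after SDF and potassium iodide and before the cement, the same conditioning step as in arm 2 (polyacrylic acid, 10–15 s). This also brings arm 1 into line with the technique described in the Introduction.
- Use one product name for the glass ionomer in both arms.
- Describe the contrast as SDF + potassium iodide + ART against ART.
- Record for each arm 1 tooth already treated whether it was conditioned. Section 2.3 has recruitment starting in August 2022 and the article appeared on 26 October 2022, so some teeth may have been treated before the text could be corrected.
- If leaving conditioning out of arm 1 is intended, say so, and word the objective and conclusions as a comparison of two treatment packages.

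The cost is one sentence in the procedure, 10–15 s of chair time per arm 1 tooth if the step is not already done, and one yes/no field on the record form. No extra participants or visits are needed.

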### 2.8. Primary Outcomes

#### 2.8.1. Assessment of Survival of the Restoration 

The follow-up will be conducted on the 7th and 30th days, and the end of the 6th month to evaluate the survival of the restoration (Table 1).

Each restoration will be assessed according to codes and criteria used in ART studies as proposed by Jo E Frencken [13]. Cavities treated with SDF and ART will be considered arrested caries lesions when the tooth surfaces with active caries at baseline visit change into surfaces with arrested caries beneath an intact restoration. The restored tooth is asymptomatic and clinically functional.

In the SDF and ART or ART-treated tooth, if caries progress beyond the dentine, it will be considered not arrested. In such conditions, the patients will be advised to follow standard treatment protocols. During the follow-up period, if the restored tooth is extracted due to infection, trauma, or fracture, the concerned tooth will not be included in the study.

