#### 2.8.2. Radiographic Evaluation of Caries Arrest of the Lesion

At the end of the 6th month, a digital radiograph evaluation of the surviving restoration will be done for comparison with the baseline radiograph. Radiographic evaluation will be done only at the end of the 6th month as it takes a minimum of 3–4 months for radiographic changes to be evident.

The digital radiographic evaluation of the restored teeth will be done by two independent blinded examiners. The efficacy of the treatment will be assessed by the presence or absence of an increasing radiolucent area below the restoration. Each radiograph will be classified using Ekstrand criteria [34].

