## 4. Statistical Methods

The observed data will be coded, tabulated, and analyzed using Statistical Package for Social Sciences (version 20). We will assess the outcomes at two levels (the Tooth level and the Individual level). The Chi-square test will be executed to assess the bivariate association between the outcome and sociodemographic variables. Kaplan–Meier survival analysis will be conducted on the censored data for the survival of the restoration. The difference between survival curves will be assessed by the Mandel—Haenszel log-rank test. Factors affecting survival rates will be assessed using the Cox-proportionality regression method. Between the two groups, the arrest of active carious lesion and survival of the restoration will be compared on the 7th day, 30thday, and at the end of the 6th month of the study visit. If there is a variation in outcome in patients with multiple restorations, tooth level analysis will be carried out.

Subgroup analysis will be performed at the tooth level (type of cavity; class1 and class 2, maxillary and mandibular teeth, premolar and molar)

We intend to have two sets of analyses.

The intention-to-treat analysis (including all randomized patients irrespective of whether they have or have not received the prescribed treatment).The per-protocol analysis.

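### Caries arrest, a primary outcome, has no single rule that classifies every tooth, and it is to be compared at two visits with no usable measurement of it

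*Protocol article*

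**What the plan says.** Sections 2.8.1 and 2.8.2 of the protocol article both stand under Primary Outcomes, and between them they give these rules.

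- **Success rule (2.8.1).** "Cavities treated with SDF and ART will be considered arrested caries lesions when the tooth surfaces with active caries at baseline visit change" to an arrested state under a filling that is still whole. The restored tooth is also described as free of symptoms and functional. The sentence names the combined-treatment arm only.
- **Failure rule (2.8.1).** For a tooth in either arm, "if caries progress beyond the dentine, it will be considered not arrested". Advice on the patient's further care follows directly.
- **Radiographic rule (2.8.2).** Efficacy is judged by the "presence or absence of an increasing radiolucent area below the restoration", comparing month 6 with baseline, by two independent blinded examiners, in surviving restorations. A cited radiographic classification is also to be applied, without saying which categories count as arrested.

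On timing, 2.8.2 says "Radiographic evaluation will be done only at the end of the 6th month", because visible change takes at least 3–4 months. Section 2.7 schedules digital radiographs of the restored tooth after the procedure and at the end of the study. The Abstract ties arrest to the baseline and month-6 radiographs, and lists day 7, day 30 and month 6 for survival of the restoration. Section 4, however, states that "the arrest of active carious lesion and survival of the restoration will be compared on the 7th day", then on day 30 and at month 6. Table 1 marks caries arrest at all three visits.

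**The concern.** A primary outcome needs a rule that puts every tooth in exactly one category, in the same way in both arms. Here the category of a tooth can depend on which paragraph the analyst uses. The teeth affected matter most: enrolled lesions are cavitated and free of pulp involvement (2.5, 2.6), so enlargement within dentine is a natural way for arrest to fail. If the choice of rule is left until the radiographs have been read, it can be made with the results in view.

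The timing raises a separate problem. A between-group comparison of arrest on day 7 or day 30 needs something to measure at those visits. If nothing valid is available, the result depends on what the examiner records for a lesion hidden by the filling. Section 2.12 says the principal investigator cannot be blinded.

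**Working it through.** No arithmetic decides this point. The sample size in 2.11 rests on an effect size of 0.4 and names no outcome. Its 100 per group is reproduced by a two-sided comparison of means at 0.05 with 80% power (99 by the normal formula; 99.08, rounded up to 100, by the t-test). None of this depends on how arrest is defined. The check is to apply each rule to the same teeth.

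**Step 1: classification at month 6**

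| Tooth | 2.8.1 success rule | 2.8.1 failure rule | Result under 2.8.1 | 2.8.2 |
|---|---|---|---|---|
| Restoration intact, lesion stable and arrested | met | not met | arrested | no increase |
| Restoration intact, lesion larger but within dentine | not met | not met | unclassified | failure |
| Restoration intact, lesion beyond dentine | not met | met | not arrested | failure |
| Restoration lost, lesion stable | not met (no intact restoration) | not met | unclassified | not evaluated |
| Restoration lost, lesion beyond dentine | not met | met | not arrested | not evaluated |

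The sections agree in the first and third rows only. In the second, 2.8.2 records a failure and 2.8.1 gives no category. In the fourth, neither section classifies the tooth. In the fifth, 2.8.1 records a failure and 2.8.2 does not look. The third row assumes that progression beyond dentine shows as increased radiolucency.

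The success rule cannot close the gap by itself, because it defines an arrested lesion as a surface that has become arrested. The cited classification does not close it either, because it is not mapped to arrested or not arrested.

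**Step 2: what can be measured at each visit**

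| Visit | Arrest compared (Section 4, Table 1) | Radiograph of restored tooth (2.7, 2.8.2) | Past the 3-month lower bound in 2.8.2 | Lesion surface open to the probe (2.6) |
|---|---|---|---|---|
| Day 7 | yes | no | no | no, covered |
| Day 30 | yes | no | no | no, covered |
| Month 6 | yes | yes | yes | no, covered |

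The only clinical test of lesion activity in the article is probe penetration (2.6), which needs access to the lesion. Under an intact restoration there is none. Two of the three planned arrest comparisons therefore have neither a radiograph nor an applicable clinical criterion.

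**Step 3: can Section 4 be read more narrowly?** Its sentence could be taken to mean survival at all three visits and arrest at month 6 only, which would match the Abstract. Table 1 rules this out, because its caries arrest row is marked at t1 and t2 as well as t3.

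**The case against.** The strongest reply is that a sound assessment is already in the article. The Abstract and 2.8.2 describe a blinded month-6 radiographic reading that covers all restored teeth regardless of arm, and 2.8.2 is the section headed for caries arrest. On this view, the sentence about progression beyond dentine sits under the survival heading and serves mainly to trigger advice on further care. The early arrest comparison would rest on one compressed sentence and a table whose intervention rows appear empty in the text at hand. Early clinical judgement might also be possible, since 2.12 trains the investigator in assessing caries cessation and 2.8.1 mentions an asymptomatic, functional tooth.

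Much of this limits the point, and three stronger readings should be set aside.

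- A reader might infer that 2.8.1 counts a lesion growing within dentine as a success. It does not. Such a lesion also fails the success rule, so 2.8.1 leaves it unclassified. A power comparison that treats it as arrested would have no basis in the text.
- A reader might infer that the arms are to be judged by different criteria, because the success sentence names only the combined treatment. The failure rule names both arms, 2.8.2 applies to restored teeth generally, and Section 4 compares the two groups. This is best read as a drafting slip.
- A reader might infer that the protocol itself says arrest cannot be seen early. Section 2.8.2 speaks only of radiographic change.

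What the reply does not remove is the failure sentence, which does use the language of arrest and sets a threshold different from that of 2.8.2. Absence of symptoms and normal function describe the tooth and restoration, not the activity of the lesion beneath. Training in caries cessation supplies no criterion for a covered lesion.

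**Conclusion.** The point holds in this form: a primary outcome lacks one consistent rule, and two of its three planned comparisons lack a usable measurement. The size is one of classification. Lesions enlarging within dentine are failures under one section and unclassified under the other, and stable lesions under lost restorations are classified by neither. How many teeth this affects cannot be derived from the article, and no stated figure changes.

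Two things can be said about direction. A threshold beyond the dentine cannot produce more failures than a threshold of any increase, provided deeper progression shows on the radiograph. And limiting the reading to surviving restorations compares selected teeth if restoration loss differs between arms.

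The conclusion rests on reading the caries arrest row of Table 1 as it appears, and on the article giving no criterion for arrest under a restoration other than the radiograph. Outcome definitions and their visit times are stated here and disagree, so this is not detail left to an analysis plan.

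**What to change.** 1. For the outcome analysis, use one definition in both arms: arrest at 6 months means no increase in radiolucency beneath the restoration between the immediate post-restoration radiograph and the 6-month radiograph, as read by the two blinded examiners already planned. Word it for both arms, and say how the cited radiographic classification maps to it.
2. State how teeth with lost restorations are counted, for example as not arrested or by reading the lesion whether or not the restoration survives. Fix the choice before the 6-month radiographs are read.
3. Stop using progression beyond dentine as the outcome threshold, and reconcile that passage of 2.8.1 with 2.8.2. Leave its patient-care advice unchanged.
4. Remove the day 7 and day 30 arrest comparisons from Section 4 and the t1 and t2 arrest marks from Table 1. Keep restoration survival, the questionnaire (2.9) and adverse-event collection (2.14) at those visits.

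The cost is an amendment of wording. The definition uses radiographs and readers already planned and needs no new visits. The drawbacks are fewer arrest comparisons and possibly a lower reported arrest percentage.

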## 2. Methods

### 2.1. Study Design

This is a randomized, controlled trial with two parallel comparator arms, having a 1:1 allocation ratio (Figure 1).

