### 2.11. Sample Size

The sample size was determined by using the G*Power statistical analysis program. With an anticipated effect size of 0.4, the probability of alpha error of 0.05, and 80% power, the sample size is estimated to be 100 per group. Expecting a 10% attrition in the follow-up visit, the final sample size per group is 110. Therefore, the total sample size is 220.

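### Extracted teeth leave both primary outcomes, and 6-month radiographic arrest is compared only among surviving restorations, so the arm comparison may be biased

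*Protocol article*

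**What the plan says.** Section 2.8 names two primary outcomes: survival of the restoration (2.8.1) and radiographic caries arrest (2.8.2).

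- **Extraction.** Section 2.8.1 states that "if the restored tooth is extracted due to infection, trauma, or fracture, the concerned tooth will not be included in the study".
- **Arrest and non-arrest.** The same section requires an intact restoration over the lesion for arrest, and scores caries that passes beyond the dentine as not arrested.
- **Teeth read at 6 months.** Section 2.8.2 states that "a digital radiograph evaluation of the surviving restoration will be done for comparison with the baseline radiograph".
- **Analysis set.** Section 4 plans an intention-to-treat analysis, "including all randomized patients irrespective of whether they have or have not received the prescribed treatment", and a per-protocol analysis. Restoration survival is analysed by Kaplan–Meier and log-rank on censored data.
- **Missing data.** Section 5 plans multiple imputation for individual dropouts and a sensitivity analysis. It mentions neither extracted teeth nor lost restorations.

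**The concern.** Both rules select teeth on events after randomisation that the treatment can affect.

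Extraction for infection is the end of the disease course that the treatment is meant to stop. Under Section 2.8.1 a tooth with caries beyond the dentine is a failure while it is retained, but disappears from the study once it is extracted for infection. Extracted teeth never become events in the survival curves and never become non-arrested lesions.

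The radiographic rule is a separate problem. Restoration survival is itself a primary outcome. If the arms differ in survival, arrest is compared between groups that randomisation no longer balances. Section 1 links incomplete caries removal to secondary caries and failed restorations, so the restorations that drop out are plausibly those over progressing lesions. If SDF prevents such failures, more teeth leave the ART arm and a benefit on arrest is understated. If SDF reduces retention, the distortion runs the other way.

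**Working it through.** **The plan's own figure.** Section 2.11 gives an effect size of 0.4, alpha 0.05 and 80% power. Read as a standardised mean difference, two-sided, n = 2(1.96 + 0.84)²/0.4², which rounds up to 99 per group; the exact t-test gives 100. Then 100 × 1.10 = 110. The stated 100 and 110 reproduce, so this point does not rest on a sample-size error.

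**Inputs for the effect of the rules.** The protocol gives no extraction, restoration-failure or arrest rates by arm. All rates below are assumptions, chosen to show a range.

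**Radiographic arrest.** Let p be the proportion of lesions progressing (25% ART, 10% SDF + ART), f the restoration-failure proportion in progressing lesions, and 3% the failure proportion in the rest.

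- Arrested under a surviving restoration: (1 − p) × 0.97, which is 0.75 × 0.97 = 72.75% for ART and 0.90 × 0.97 = 87.30% for SDF + ART.
- All teeth kept, failures scored as not arrested: 87.30 − 72.75 = 14.55 points, whatever f is.
- Survivors: p(1 − f) + (1 − p) × 0.97.
- Survivors-only arrest: arrested divided by survivors.

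| f | Survivors, ART v SDF + ART | Survivors-only arrest | Difference (points) |
|---|---|---|---|
| 10% | 95.25% v 96.30% | 76.4% v 90.7% | 14.3 |
| 20% | 92.75% v 95.30% | 78.4% v 91.6% | 13.2 |
| 40% | 87.75% v 93.30% | 82.9% v 93.6% | 10.7 |
| 60% | 82.75% v 91.30% | 87.9% v 95.6% | 7.7 |

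The shortfall against 14.55 points runs from about 0.3 to 6.9 points.

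**Equal failures.** With 2 extracted, 8 lost and 90% arrest under intact restorations per 100 teeth in each arm, survivors-only arrest is 81/90 v 81/90 and all-teeth arrest is 81% v 81%. Both differences are zero.

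**Extraction and the survival outcome.** Suppose 10% of restorations are lost from retained teeth in each arm, and 1% v 5% of teeth are extracted (SDF + ART v ART).

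- As written: 0.89/0.99 = 89.9% v 0.85/0.95 = 89.5%, a difference of 0.4 points.
- Extractions counted as failures: 89% v 85%, a difference of 4 points.

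**The passages side by side.** Section 2.4 admits people with one or more lesions. A participant whose only treated tooth is extracted is in the intention-to-treat set of Section 4 and out of the study under Section 2.8.1. Both cannot hold. A restoration lost from a retained tooth cannot meet the arrest definition in 2.8.1, yet 2.8.2 leaves it unread rather than scored as not arrested.

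**The case against.** **A reader might infer that the worst failures all leave both primary outcomes.** They do not. Only extracted teeth leave both. A restoration that fails in a retained tooth is still scored at day 7, day 30 and month 6 and enters the survival analysis.

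**A reader might infer that the plan could show no effect at all when SDF works.** Take 100 teeth per arm, with 84 (ART) v 95 (SDF + ART) restorations surviving and 80 v 90 lesions arrested. Survivors-only arrest is 80/84 = 95.2% v 90/95 = 94.7%, so arrest looks equal. But survival, also primary, differs by 11 points (chi-square p about 0.011), unless nearly all the losses were extractions. The effect would be seen, though not on arrest.

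**A reader might infer that bias is certain and its direction known.** The documents do not support that. The large distortion above needs restorations to fail in 40% to 60% of progressing lesions. At 10% to 20% the shortfall is about 0.3 to 1.4 points. Extractions within six months may also be few, since teeth with pulpal involvement are excluded at entry.

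**The protocol is not uniform on which teeth are read.** Section 2.7 plans an end-of-study radiograph of the restored tooth, and 2.8.2 goes on to speak of restored teeth generally. Section 4 and Table 1 also schedule arrest at the earlier visits, so arrest is not only a radiographic reading. Intention to treat is defined by patient, the extraction rule by tooth. This makes part of the conflict an unreconciled gap rather than a flat contradiction.

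These limits stand. They do not rescue the rules: the extraction sentence is explicit, imputation is stated only for individual dropouts, and whether failures differ by arm is what the trial tests, so the analysis cannot assume that they do not.

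**Conclusion.** The concern holds in a limited form. The extraction rule removes some treatment failures from both primary outcomes and conflicts with the non-arrest rule in 2.8.1 and with the intention-to-treat statement in Section 4. The surviving-restoration rule separately makes the radiographic arrest comparison conditional on the other primary outcome.

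The arm comparison may be biased. On the assumed rates, a 14.55-point arrest difference appears as anything from 14.3 down to 7.7 points, and a 4-point survival difference can shrink to 0.4. The distortion is nil if failures are equal across arms and equally related to arrest. Neither size nor direction can be derived from the protocol. A larger sample would not remove the problem, so it should be corrected before the data are analysed.

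**What to change.** 1. Delete the extraction exclusion in 2.8.1.
2. In the intention-to-treat analysis keep every treated tooth. Count extraction for infection, or for fracture of the restored tooth, as a survival event and as not arrested. State separately how extraction for unrelated trauma is handled, for example by censoring.
3. For the main 6-month arrest comparison, apply the definition already in 2.8.1, which requires an intact restoration, so that lost restorations count as not arrested.
4. Keep survivors-only radiographic arrest as a supportive analysis.
5. Reconcile 2.8.1 and 2.8.2 with Sections 4 and 5, and say that the imputation does not apply to teeth with a known failure.

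The cost is wording only, with no added visits or radiographs. Observed arrest and survival percentages become slightly less favourable. A restoration lost mechanically over an inactive lesion counts as an arrest failure, and the same loss then enters both primary outcomes; the supportive analysis shows radiographic arrest apart from such losses. Another pre-stated way of handling these events would be legitimate, provided that treated teeth are not dropped from the main comparison.
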